### 5.3 Eligibility Assessment

Following an expression of interest volunteers will be invited to the Human Nutrition Unit (HNU) for a preliminary interview and given further details of the study.

The volunteers will be encouraged to ask questions at this point prior to making any commitment. At the end of the interview all volunteers will be given a minimum of 72 hours *(*3 days) to consider whether they wish to participate in the study. They will be given a small sterile container to take away with them. If they wish to participate, this container will be used for the urine sample on the morning of the clinical screening visit. If they decide they do not wish to take part in the study they will be told to discard the container. During this consideration period the volunteers will not be contacted. If, following this period of consideration, the volunteer still wishes to participate they will be asked to contact [name] [name] [name] or [name] [name]*.* If the volunteers are very keen to take part in the study, a date for their screening can be booked at the interview stage. The date agreed upon will be after the 72hours (3 days) consideration time has elapsed.

## 5.4 Clinical/Eligibility screening

All those responding positively will be invited to attend the HNU for a clinical screening following an overnight fast (8 hours*)*. Volunteers will be advised that they should drink water during this fasting period. They will be reminded to bring a midstream sample of urine from the first urine of the morning in the container provided at the first interview. Volunteers need to arrive within 2 hours after collection of the urine sample as this is a required specification for the validity of the urine dipstick test. The urine samples will not be tested until after the consent forms (annex 5+5a) have been signed. As there is an option for the volunteer to take part in the faecal collection, there will be a separate consent form for this.

On arrival at the HNU the study scientist will go through the consent forms with the volunteer and encourage any questions they may have at this stage. Due to the optional nature of one part of the study (the collection of faecal samples to examine the effects of selenium on DNA methylation) the volunteers agreeing to take part in this will then be asked to sign an extra consent form. A medication declaration form (annex 6) agreeing to inform the study scientist of any medication they may have to take will also be signed. A copy of these forms will be given to the volunteer to keep. A qualified nurse will then complete a screening questionnaire (annex 7) take and record blood pressure, pulse, height and weight measurements, calculate Body Mass Index (BMI), perform the urine dipstick test (Combur 9 Test®, Roche Diagnostics Ltd). An 8mL blood sample will be taken for Full Blood Count (FBC) and glucose analysis. The blood sample will be sent to the BUPA hospital for analysis. A further 7mL of blood will be used for serum (or plasma) selenium determination which is the major part of the screening process. The analysis of the serum samples will take place on a weekly basis at the end of a week of screenings. The system of analysis can be run whether two volunteers are screened in one week, or twenty. The results from the analysis will usually be known on the day and so the volunteers will not be kept waiting to hear if they have passed the study or not. The volunteers will be made aware of the fact that even though their blood results may be within range, they may be excluded from the study due to inappropriate selenium status.

The urine results (annex 8) will be known immediately. If any of the results for the urine dipstick test are outside the reference range the nurses will refer to the Protocol for Abnormal Urinalysis Results which provides advice on exclusion or re-screening of the volunteer. This protocol has been authorised by the HNU Medical Advisor.

If the BMI is <18.5 or >35 the volunteer will be excluded from the study. If any of the results for the screening blood tests fall outside the standard reference ranges they will be assessed by the HNU Medical Advisor as to whether the results could affect the study data or have implications for the health of the volunteer, and therefore whether inclusion, re-screen or exclusion is appropriate. The HNU Medical Advisor may say that even though results are outside the reference ranges, either a re-screen or inclusion may be appropriate, since some minor deviations will not warrant a re-screen and will neither affect the study data nor have health implications for the volunteer.

If a re-screen is considered appropriate the volunteer will be given the option of returning for another blood test after a period of two weeks. Volunteers who do not wish to be re-screened or who display screening parameters outside the standard reference ranges on both occasions will be excluded from the study.

Copies of all clinical results will be sent to the volunteer’s GP (a letter to GP accompanying clinical results that have passed the screening-Annex 10) and in the event of flagged results (a letter to GP accompanying clinical results that have not passed the screening-Annex 11) the volunteer will be notified by letter (letter to volunteer informing them that they have not passed the screening and that they should contact their GP-Annex 12) advising them to speak to their GP to discuss the results. Results will not be discussed with the volunteer.

Volunteers who meet the study criteria and whose screening results are satisfactory will be contacted and offered appointments at the HNU to continue with the study. The GPs of those successfully recruited onto the study will be informed of their patient’s participation in the study by letter (annex 9) and will be sent copies of all clinical results. As the study involves the administration of the flu vaccine, the letter will also ask the volunteers GP if there is any reason why the volunteer should not be having the vaccine. The GPs will be asked to contact the study team if there is any contraindication. The volunteer will agree to this information being sent to the GP by signing the consent form(s) (Annex 5 and/or 5a). If there is any contraindication, the volunteer will not be allowed to continue with the study and will therefore be excluded. A letter would then be sent to the volunteer explaining this (Annex13). Once the flu vaccine has been administered a copy of the vaccination record, completed by the HNU research nurses, will be sent to the GP.

Once recruited onto the study, volunteers will be assigned a code. The information linking codes to volunteers will have restricted access. All personal information will be kept confidential and known only to the Principal Researcher and project leader, HNU research nurses, the volunteer’s GP and the HNU medical advisor.

## 6.0 Study Protocol

## Due to the nature of the study (onions only available in year 2 and 3) and the fact that some volunteers may have a dislike or intolerance to onions it would be difficult to fully randomise the study and unethical to accept those volunteers onto the onion part of the study. In year 2 and 3, which includes the onion, intervention, volunteers with no dislike of onions will be randomly allocated to one of six groups.  Volunteers with a dislike of onions will be randomly allocated to one of four groups.  There is no evidence to suggest that volunteers who do not or cannot eat onions will display any differences in immune function response or selenium status to those volunteers that do, and thus there will be no consequences of the study not being fully randomised.  However, as this is a new area of research, the preferences of all subjects recruited in the first year of the study will be monitored, and the possibility of differences by onion “preferences” investigated.

## Volunteers will be stratified by sex.

## 6.1 Supplementation Intervention with Se-yeast

Se-yeast supplementation (groups 1-4) will be studied during years 1, 2 and 3 of the project. All the pressed tablets will be identical (bar alphabetical labelling which will be carried out at manufacture) and will be labelled according to the law. Safety advice will also be given when the tablets are handed to the volunteers. One tablet will be taken each day for 12 weeks. The volunteers will also be given a record sheet where they will be asked to indicate at which times the supplement was taken each day (Annex 16).

Group 1: Se-yeast tablet (50μg Selenium/day)

Group 2: Se-yeast tablet (100μg Selenium /day)

Group 3: Se-yeast tablet (200μg Selenium /day)

Group 4: Placebo (control group).

On Day 1 of the study, the volunteer will be asked to attend the unit in the morning between the hours of 7:30 and 9:00am to give their first fasting blood and saliva sample. A scientist from the study team will be on hand to ensure that the volunteer is relaxed and comfortable. The volunteers will be asked not to brush or floss their teeth prior to arriving at the Unit as the use of toothpaste may interfere with the saliva sample to be collected. The volunteer will however be encouraged to bring their toothbrush and tooth paste with them to the unit so they may brush their teeth at an appropriate time, when all samples have been taken. All phlebotomy will be carried out by a qualified nurse at the HNU. A baseline venous sample of 80mL will be obtained for later determination of full blood count and glucose, as well as plasma (or serum) selenium levels, selected selenoenzyme activity, key selenium-responsive genes and protein levels and immune function markers**.** A saliva sample will also be collected from the volunteers after the blood has been taken, so the volunteer can stimulate their saliva glands by chewing sugar free gum while their blood is being taken. The volunteer will be asked to rinse their mouth out twice with cool water before chewing the gum and subsequently producing the saliva sample. The saliva samples will be used totest for a baseline of antibody titres to influenza antigens.

After the consumption of a standard unit breakfast (a range of cereals, toasted bread, tea or coffee), the volunteer will be supplied with a 6 week supply of their Se-yeast tablets and a container for carrying out a 24hour urine collection prior to their next visit in week six. The volunteer will not know what dose of selenium they will have been given neither will the scientist (double blind).The volunteer will be advised to take one tablet everyday for the next 6 weeks, preferably with meals. The volunteer will be given a record sheet to indicate at which time of each day they are taking their supplement. The volunteer will be advised to contact either [name] ([name]) or [name] ([name]) if they have any queries or problems associated with the Se-yeast tablets.

[figure not shown]
Prior to the start of week six (Day 42±2days), the volunteer will be contacted by telephone or e-mail and reminded when to start their 24hour urine collection, which they will bring with them when invited to the Institute again in the morning between the hours of 7:30 and 9:00am for their second fasted blood sample. No saliva sample will be collected in week 6.

**Figure 2: The deltoid muscle**

The volunteer will again be given a standard breakfast. The volunteer

will then be given their second batch of Se-yeast tablets which will cover their supplementation until the end of the study (week 12).

At the start of week ten, (day 70±2days), the volunteers will come in for their 3rd fasted blood sample in the morning between the hours of 7:30 and 9:00am. The blood sample (80mL) will be taken and before the volunteer is given their standard unit breakfast. They will be given their flu vaccine at the HNU by the qualified nursing staff. The preferred site of administration in adults is the deltoid muscle.

Please note that volunteers will be asked to inform us if they suffer from a cold at the time of the scheduled flu vaccination. If this is the case then we will re-schedule the vaccination appointment. Volunteers will be asked to continue taking the supplements or onion meals as before. In the unlikely event that a volunteer feels unwell for more than 2 weeks we will have to exclude him/her from further study participation.

After the administration of the flu vaccine, the volunteer must remain in the HNU for at least 20minutes and preferable consume breakfast. This is to ensure that there is no anaphylactic response following vaccination. After the standard unit breakfast has been consumed the volunteers will continue to take the Se-yeast capsules as per usual. The volunteer will return to the unit to give fasted blood samples 7 (week 11) and 14 (week 12) days post vaccination (80mL each time); a saliva sample in week 12 and again the volunteer will have the option of producing a faecal sample in week 12. The same procedure will be followed for the collection of the faecal sample in week 12 as prior to week 1. All samples produced until 7pm will be collected from the volunteer’s home by a member of the study team. Volunteers who produce samples after this time will be asked not to collect. The completion of a 12 week Se-supplementation period will mark the end of the volunteer’s participation in the study.

Uncertainty about delivery dates for flu vaccines cause logistical problems. We cannot delay the supplement/dietary intervention until we have confirmation of the delivery date of the flu vaccine. We also need to achieve a continuous flux of volunteers as we are limited to the number of immune function assays we can manage per week. In each project year the first volunteers start the intervention in July so that week 10 (vaccination) falls into the second half of September a date that was originally be considered feasible for the flu vaccine to be available after having contacted several suppliers. However, a delay in flu vaccine deliveries is a possibility and our suggestion is to allow for some flexibility if this happens. We suggest that volunteers that reach week 10 may continue with supplement/onion meals for a maximum of 3 more weeks if the flu vaccine is not available. If the flu vaccine is still not available at week 13 then a final blood sample will be taken for biomarker and immune function analysis. This approach still allows us to complete our measurements of selenium biomarkers but is less likely to show any effect with respect to immune function. However, this should only affect a limited number of volunteers. How many is difficult to predict as we don’t know for some time when the flu vaccine will be available. We feel that this approach is an acceptable solution as we will still meet all the objectives related to plasma selenium status and biomarkers of selenium status.

**Further, we also suggest extending the current flu vaccination period (September to February) to include March and April 2007 and 2008. We will always endeavour to not vaccinate in March and April but we are dependent on the actual flu vaccine delivery for the life time of this project. The HRGC protocol (Annex 1) and volunteer information (Annex 4) have been amended accordingly.**

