Intakes of selenium in the UK have fallen from a mean of 60μg/day in 1974 to 30-40μg/day in recent years (Ysart et al, 1999) mainly due to the replacement of Canadian wheat (high in selenium) with European wheat (low in selenium); this has resulted in a fall in the mean plasma selenium concentration (Rayman, 1997). One of the proposed consequences of marginal selenium status is impaired immune function. As people age, they are more prone to infections and tumours and this is, at least in part, related to a decline in immune function. One effect of ageing on T lymphocytes is a shift towards a T-helper 2 (Th2) response during an infection, which means a reduced production of Th1 cytokines such as interleukin-2 (IL-2) and interferon-gamma (IFN-) (Cakman et al, 1996). In addition, natural killer (NK) cells, responsible for recognising and killing tumour and virally infected cells, exhibit an age-associated decline in activity, particularly in their ability to proliferate and to kill NK-resistant cell lines in response to IL-2 stimulation (Solano et al, 1999). As a direct consequence of this age-related decline of immune effectiveness, infectious diseases remain a significant cause of morbidity and mortality in the elderly. In particular, influenza virus is a globally very important contagion for the elderly (Nicholson et al, 2003) and few other diseases exert such huge toll in terms of suffering, medical consultation, hospital admission and economic loss (CDC-USA, 2003; Thompson et al, 2003).

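### Volunteers excluded for illness lasting over two weeks around vaccination get no closing selenium sample, although volunteers left unvaccinated by supply delays do

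*Protocol*

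**What the plan says.** Both provisions stand in Protocol section 6.1, in the text after the Figure 2 caption. Section 6.2 applies the same week-10 procedure to the onion groups.

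**Illness.** At the week-10 visit "volunteers will be asked to inform us if they suffer from a cold at the time of the scheduled flu vaccination". The appointment is then moved, and the intervention goes on: "Volunteers will be asked to continue taking the supplements or onion meals as before". If the illness persists: "In the unlikely event that a volunteer feels unwell for more than 2 weeks we will have to exclude him/her from further study participation". Nothing is said about a last sample.

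**Late vaccine supply.** Here "volunteers that reach week 10 may continue with supplement/onion meals for a maximum of 3 more weeks if the flu vaccine is not available". After that: "If the flu vaccine is still not available at week 13 then a final blood sample will be taken for biomarker and immune function analysis". The reason given is: "This approach still allows us to complete our measurements of selenium biomarkers but is less likely to show any effect with respect to immune function".

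Section 7.0 names week 12 as the time point of primary interest.

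**The concern.** Both provisions concern a volunteer who has been randomised, has taken about ten weeks of the allocated intervention and has not been vaccinated. One such volunteer is followed to a closing sample and the other is not. The reason stated for the closing sample is that selenium status can be measured without vaccination, which is as true of the ill volunteer.

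The difference matters because the two causes are not alike. Late delivery has no evident link to the allocated arm. Prolonged illness might have one, on the protocol's own reasoning. The plan thus keeps the volunteers whose missing vaccination is plausibly unrelated to treatment and stops following those for whom that is less sure. At stake is an end-of-study selenium result for each such volunteer, and a count of exclusions that could go unnoticed by arm. A statistical analysis plan cannot repair this afterwards, because it cannot analyse a sample that was never taken.

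**Working it through.** The plan states no figure on this point, so the check is mainly a comparison of the texts.

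**1. Timing.** The vaccination visit is on day 70 ± 2 (section 6.1), and the illness threshold is 2 weeks, or 14 days.
- Counted from the scheduled visit: 70 + 14 = 84 = 12 × 7, so day 84, with a range of 82 to 86.
- A volunteer who falls ill at that visit and continues the intervention as instructed has therefore reached about week 12 when the threshold is passed. If the illness began earlier, the threshold is passed correspondingly earlier.
- The supply provision runs to week 10 + 3 = 13, or day 91. Its closing sample is thus taken 7 days after day 84.

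**2. Side by side.**

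| | Illness over two weeks | No vaccine at week 13 |
|---|---|---|
| Randomised | yes | yes |
| Vaccinated | no | no |
| Intervention while waiting | continues | continues |
| Closing blood sample | none foreseen | yes |
| Stated reason | none | selenium biomarkers can still be measured |

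**3. Does the reason carry over?** Section 6.31 divides the study-day blood into 3 + 10 + 15 + 12 + 40 = 80 mL. The 40 mL part is for the immune assays and is left out at week 6, so 80 − 40 = 40 mL is drawn then. The selenium, selenoprotein and RNA portions do not depend on vaccination. The reason carries over in full for selenium status.

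**4. What is lost.** Five study samples are planned, at weeks 0, 6, 10, 11 and 12.
- Weeks 0 and 6 are already in hand.
- Week 10 is planned just before the injection. The text does not say whether it is still taken when the appointment is moved.
- Weeks 11 and 12 are set at 7 and 14 days after vaccination and are lost.

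Two or three of the five samples remain, and none of them is at the time point of primary interest.

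**5. Could the loss depend on arm?** Section 2.0 says "One of the proposed consequences of marginal selenium status is impaired immune function" and links older people's proneness to infection partly to immune decline. Section 3.0 makes resistance to influenza an objective. A link between arm and prolonged illness is an inference, but one that the protocol's rationale allows.

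**6. Size.** The shift in an arm's mean from losing some volunteers is (proportion lost) × (mean of those kept − mean of those lost). A comparison between arms is biased only as far as this product differs between them. The documents give neither factor, so no value can be put on it. The drop-out allowance in section 7.0 is arithmetically consistent, 18 / (1 − 0.25) = 24 per group, but it protects numbers and not against selective loss. Section 5.0 recruits until 144 have completed, so excluded volunteers are made up in number by completers.

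**The case against.** The strongest reply is that the two provisions concern different people. One volunteer is well and waiting for stock; the other has been ill for more than two weeks. Sparing the latter a fasted blood draw is a welfare decision, and illness may disturb the assays. The rule is the same in every arm, allocation is double-blind, and the event is described as unlikely. This stands as far as it goes: the provisions do not contradict each other outright, and nobody should be sampled against clinical judgement. It does not explain why no sample is even offered to someone willing and fit.

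A reader might also infer more than the text supports:

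- *That these volunteers are removed from the trial altogether.* The wording ends further participation. It does not discard what has been collected, and section 7.0 plans a repeated measures analysis that could use the earlier visits.
- *That they are excluded for poor immune function.* The text refers only to feeling unwell, so any illness counts.
- *That the immune comparison is materially biased.* This needs an assumed number of exclusions, concentrated in one arm, and an assumed deficit in response. The documents supply none of these.
- *That a closing sample would rescue the immune results.* A volunteer who was not vaccinated has no vaccine response to measure. Nor does anything in the protocol support scoring a long illness as a poor response.

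**Conclusion.** The point holds in a limited form. As written, section 6.1 gives up the end-of-study selenium-status measurement for volunteers excluded through illness, although the protocol's own reason for sampling other unvaccinated volunteers applies to them. The loss comes after randomisation, and its cause could differ by arm.

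What is certain is the loss of one end-of-study selenium result per excluded volunteer. Any bias is probably small, because the event is expected to be rare, and it cannot be quantified because no frequency is given. That the exclusions might be uneven rests on the rationale in section 2.0 and not on data. This is a minor weakness that is cheap to remove, and it does not threaten the trial's validity.

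**What to change.** Reconcile the two provisions of section 6.1 on follow-up, leaving decisions on vaccination and continued intervention to the investigator. A short addition would do:

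- Offer a volunteer excluded for prolonged illness, if willing and fit, the final fasted sample already foreseen for supply delays.
- Keep the volunteer in the randomised arm for the selenium-status analysis, using all samples collected.
- Report the number of such exclusions by arm alongside the immune results.

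The cost is a few lines of text and one visit per affected volunteer, which some will decline. The change does not recover the vaccine response. For the immune outcomes it only lets a reader see whether the exclusions were uneven.

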In order to allow for the unlikely possibility of a year effect the control group and each of the three selenium supplementation groups will be evenly and randomly spread over the three years. Unfortunately due to time constraints, this is not possible with the onion groups which will be evenly and randomly spread over only two of the years (i.e. half in each year). The two onion groups will also be able to be analysed separately, but with a reduced power of 18 subjects per group gives a power of 80% of detecting a difference in response variable of 1 standard deviation. This is quite a large effect of the enriched onions, given that they are only “equivalent” to a selenium dose of 50µg/day. This is based on a 25% drop out rate expected for the onion intervention study.

The data would be initially analysed using an ANOVA model to test for differences in end-points between the groups. If the required data assumptions for this model are not met (e.g. normality), then data transformations and/or non-parametric methods will be employed. A repeated measures analysis using all 5 data points per subject will also be used, although it is the end-point (week 12) that is of primary interest.

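### Week 12 and 14 days post vaccination are treated as one time point, but permitted vaccine delays separate them, and the protocol does not say which defines the immune end-point or whether unvaccinated samples count

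*Protocol*

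**What the plan says.** **Standard schedule (Protocol section 6.1, text around Figure 2).** "At the start of week ten, (day 70±2days), the volunteers will come in for their 3rd fasted blood sample", and the vaccine is given at that visit. The volunteer then returns for "fasted blood samples 7 (week 11) and 14 (week 12) days post vaccination (80mL each time"). Section 6.2 repeats this for the onion groups. Section 6.1 closes the schedule with: "The completion of a 12 week Se-supplementation period will mark the end of the volunteer’s participation in the study".

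**Two routes to a later vaccination (section 6.1).** For a volunteer with a cold: "If this is the case then we will re-schedule the vaccination appointment". For late vaccine delivery: "volunteers that reach week 10 may continue with supplement/onion meals for a maximum of 3 more weeks if the flu vaccine is not available".

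**No vaccine at all (section 6.1).** "If the flu vaccine is still not available at week 13 then a final blood sample will be taken for biomarker and immune function analysis". The protocol concedes that this makes an immune effect harder to show. It expects few volunteers to be affected but says that the number is hard to predict.

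**Analysis (section 7.0).** End-points are compared between groups by ANOVA. A repeated measures analysis of all five time points is added, "although it is the end-point (week 12) that is of primary interest".

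**Outcome (section 2.0).** The immune outcomes are cellular and humoral responses to influenza vaccine.

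**The concern.** Two clocks run in this trial: weeks since the start of the intervention, and days since vaccination. They agree only when vaccination happens at week 10. The protocol permits later vaccination, and in one branch none, without saying what then becomes of the end-point.

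Three things are at stake.

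- **Comparability.** Immune values labelled week 12 could come from different times relative to vaccination. If day 14 is used instead, volunteers could have different lengths of selenium exposure.
- **Missing visits.** If participation ends at 12 weeks as written, a volunteer vaccinated late has no clearly scheduled day-14 visit. An analysis plan cannot recover a sample that was never taken.
- **Dilution.** A sample from a never-vaccinated volunteer holds no response to the vaccine. Pooling it with vaccinated samples pulls the groups together on that outcome.

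**Working it through.** **1. The planned schedule reproduces.** Vaccination at week 10 plus 14 days is week 12.

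**2. The permitted delay.** Section 6.1 allows up to 3 more weeks, so vaccination can fall at week w = 10 to 13. Days since vaccination at intervention week 12 are (12 - w) × 7. The 14-day sample falls at week w + 2.

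| Vaccination week | Intervention week 12 relative to vaccine | Week of the 14-day sample |
|---|---|---|
| 10 | day +14 | 12 |
| 11 | day +7 | 13 |
| 12 | day 0 | 14 |
| 13 | day -7 | 15 |

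The middle column applies if week 12 is counted strictly from the start of the intervention. The right-hand column applies if the sample follows the vaccine. Both differ from the plan as soon as w exceeds 10.

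**3. The passages side by side.** Section 6.1 ends participation at 12 weeks, yet the delay rule keeps volunteers on the intervention to week 13, and the no-vaccine rule takes a final blood sample then. Neither rule restates the post-vaccination visits or the end of participation. Section 6.34 schedules saliva by weeks 0 and 12 only, while section 4.1 calls the week-12 saliva post-vaccination. Section 7.0 uses both clocks: its standard deviations for the antibody measures are for day 7 post vaccination, and its time point of primary interest is week 12.

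**4. Size of the dilution (illustration).** Let u be the share of end-point samples from never-vaccinated volunteers, equal in all arms, with no selenium effect on the outcome in those samples. Group differences are multiplied by (1-u): 1 SD becomes 0.9 SD at u = 10% and 0.8 SD at u = 20%.

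For power, section 7.0 gives a six-group one-way ANOVA, a range of 1 SD, effects proportional to dose, and 24 per group falling to 18 after 25% drop-out. The alpha level is not stated; I assume 0.05.

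- Drop-out step: 18 / (1 - 0.25) = 24, as stated.
- Means in SD units: 0, 0.25, 0.5, 1, 0.25, 0. Their mean is 2/6 = 0.333. The sum of squared deviations is 1.375 - 6 × 0.111 = 0.708.
- Noncentrality = n × 0.708: 12.75 for n = 18 and 17.0 for n = 24.
- Power at n = 18 is 77%, against the stated 80%; 19 per group gives 79.9%. This small gap is a separate matter and does not bear on the point.
- Pooling multiplies the noncentrality by (1-u)².

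| u (assumed) | Power, 18 per group | Power, 24 per group |
|---|---|---|
| 0 | 77% | 90% |
| 5% | 72% | 86% |
| 10% | 67% | 81% |
| 20% | 55% | 70% |

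These figures add no variance for mixing vaccinated and unvaccinated values. If vaccination also shifts the mean by 1 SD, the variance becomes 1 + u(1-u). At u = 10% that is 1.09, and power is 62% (18 per group) or 77% (24 per group).

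**5. Pooling against leaving out.** Leaving the unvaccinated samples out reduces n by (1-u), so the noncentrality falls by (1-u) and not by (1-u)². At n = 18 and u = 10%: 12.75 × 0.9 = 11.5 when left out, and 12.75 × 0.81 = 10.3 when pooled.

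**6. Year and arm.** Section 6.4, Table 1 plans 32 supplement volunteers in each of three years, which is 8 per group per year, and 12 per onion group in years 2 and 3 only. If a share s of one year's volunteers goes unvaccinated, a year-1 shortage affects s × 8/24 = s/3 of each supplement group and none of the onion groups. A shortage in year 2 or 3 affects s/3 of each supplement group and s × 12/24 = s/2 of each onion group.

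**The case against.** **Blood samples are anchored to vaccination.** Section 4.1 (text below Figure 1) places the later blood samples 7 and 14 days post vaccination with no week number. Sections 6.1 and 6.2 give the week only in brackets. A reader might infer from the delay rule that some end-point samples are certain to be taken before the vaccine. The documents do not support that: day 0 and day -7 arise only on a strict intervention-week reading. This part of the objection stands. What remains is that section 7.0 names week 12, section 6.1 ends participation at 12 weeks, and nothing says which clock governs after a delay.

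**The delay rule is a specific exception to the 12-week end.** It would be odd to wait for the vaccine and then take no blood. That is a fair guess at the intent, but the visits are not written down.

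**The no-vaccine branch is disclosed, and some immune assays do not need vaccination.** Cytotoxicity, cytokine production in culture and NF-kB can be measured in an unvaccinated volunteer. The sample is also taken at week 13, and the protocol does not say that it enters the week-12 ANOVA. All of this stands, so dilution follows only if the samples are pooled. An unseen SAP may settle the analysis sets. It cannot settle visit timing or the end of participation, which are protocol content.

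**The size is assumed.** The protocol gives no u. The dilution applies to never-vaccinated volunteers, not to those vaccinated late, and plasma selenium does not depend on vaccination. The cold route is partly bounded, because anyone unwell for more than 2 weeks is excluded. These limits stand.

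**Conclusion.** The protocol uses two time scales as one and then permits them to diverge. With vaccination as late as week 13, day 14 falls as late as week 15, beyond the stated 12-week end of participation. For delayed volunteers the immune end-point is undefined. On the intervention clock, a week-12 sample could precede day 14 or even the vaccine; on the vaccine clock, selenium exposure is up to 3 weeks longer than planned.

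The never-vaccinated branch sends week-13 samples to immune function analysis although the outcome is response to vaccine. If pooled, they shrink the vaccine-response difference by about (1-u), assuming no selenium effect in them. The values of u shown are illustrations.

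A reader might also infer that missing vaccination is unrelated to arm because supply is external. Across the six groups that does not follow: the onion groups run only in years 2 and 3, so a shortage in one year reaches the arms in different proportions.

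The selenium-biomarker comparisons are not undermined by the absence of vaccine, although the length of exposure would vary.

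**What to change.** - In section 7.0, define the vaccine-response end-points by days since actual vaccination (day 7 and day 14), whatever the intervention week. Apply the same definition to saliva in section 6.34.
- Reconcile sections 6.1, 6.2 and 7.0 on which visits take place, and when participation ends, for a volunteer whose vaccination is delayed. How that is settled clinically is for the investigators.
- Keep never-vaccinated volunteers in the selenium-biomarker analysis. Report their immune data separately and leave them out of the vaccine-response comparison.
- Account for year in the vaccine-response comparison, because the share without vaccine could differ by arm through year.
- Record the date of vaccination and the weeks of intervention completed by then, and use this in a sensitivity analysis.

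The cost is protocol wording, one date field and slightly fewer volunteers in the vaccine-response analysis. Those left out carry no information on response to the vaccine.
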